## Abstract

**Background:**

Radical antegrade modular pancreatosplenectomy (RAMPS) has been proven to improve R0 resection and lymph harvest in treating patients with distal pancreatic cancer. The development of minimally invasive surgery has advantages in postoperative recovery. Therefore, minimally invasive (MI-) RAMPS may combine the advantages of both benefits to improve survival. Nevertheless, evidence to validate the safety and efficacy of MI-RAMPS is limited.

**Method/Design:**

The MIRROR trial will be the first multicenter prospective randomized clinical trial to investigate the outcome of MI-RAMPS. The hypothesis is that MI-RAMPS is superior in postoperative recovery. The primary outcome is the length of postoperative stay. Based on the hypothesis and primary outcome, the sample size is 250 patients (125 participants in each group). The trial will investigate factors related to surgical safety, short-term outcome, pathological assessment, and survival as secondary outcomes.

**Conclusion:**

This study will offer a relatively higher level of evidence to further illustrate the accessibility and benefits of MI-RAMPS for the treatment of distal pancreatic cancer.

**Clinical Trial Registration:**

Clinicaltrials.gov, NCT03770559.

## Introduction

Distal pancreatic cancer is a poorly-diagnosed disease with the highest incidence-to-mortality ratio worldwide (1, 2). The high incidence-to-mortality ratio is mainly due to delayed diagnosis, which limits treatment efficacy and options (3). Most recent consensus and guidelines recommend surgical resection if the primary tumor is resectable or borderline-resectable after neoadjuvant chemotherapy (3, 4). However, conventional distal pancreatosplenectomy (CDPS), which was recommended as one of the standard procedures for distal pancreatic cancer, has been reported to have unsatisfactory oncological outcomes in patients in recent years (5–7).

Accordingly, Strasberg et al. proposed radical antegrade modular pancreatosplenectomy (RAMPS) as one of the improved procedures for distal pancreatic cancer (8, 9). When compared with CDPS (5, 7, 10, 11), the procedure does not increase perioperative risks. Additionally, the expanded clearance of RAMPS results in better R0 resection rates and lymph node retrievals than CDPS. Therefore, compared with CDPS, RAMPS has been proven to be a safe procedure with better survival for patients with pancreatic cancer.

In the era of enhanced recovery surgery, minimally invasive surgery (MIS) has been widely accepted in the treatment of the most benign or low malignancy neoplasms of the pancreas (12). Nevertheless, the applicability of MIS in treating pancreatic cancer is controversial. The surgical outcomes and oncological safety of open and MIS procedures are of great interest among pancreatic surgeons. On the one hand, MIS is considered to result in less pain and shortened recovery time for the following anti-cancer treatments (13, 14). On the other hand, some malignant pancreatic cancer removals, such as RAMPS particularly, often have expanded surgical areas with the potential of more aggressive resection (8, 9).

In a previous study, we reported that the RAMPS cohort had a higher survival rate than the CDPS cohort (15). Subsequently, we performed a retrospective comparison between minimally invasive RAMPS (MI-RAMPS) and open RAMPS and found that MI-RAMPS is safer and has the potential advantages of faster recovery (16). Nevertheless, no prospective randomized clinical trial on the advantages of MI-RAMPS has been conducted. Therefore, the MIRROR study aims to conduct a multicenter, randomized controlled study to compare MI-RAMPS and open RAMPS (O-RAMPS) in treating patients with distal pancreatic cancer. This study will offer higher level evidence to pancreatic surgeons on the optimal use of MI-RAMPS to improve patients’ postoperative recovery and combine with neo-/adjuvant therapy for better survival.

## Method

### Design

The MIRROR trial is a randomized controlled, parallel-group, multicenter, superiority trial investigating and comparing the safety and effect of MI-RAMPS and OP-RAMPS for pancreatic cancer (**Figure 1**). Eligible patients will be randomly assigned to either the MI-RAMPS or O-RAMPS treatment group. This trial protocol is based on the SPIRIT guidelines and checklist (17).

**Figure 1 f1:**
[figure not shown]
Study flowchart of MIRROR study.

### Study population

This study involves eight high-volume pancreatic surgery centers in China. Each participating center has performed >200 MI/O-RAMPS cases. All patients with suspected left-sided pancreatic cancer visiting outpatient clinics of these centers will be thoroughly evaluated according to the inclusion and exclusion criteria of the study.

### Inclusion criteria

The inclusion criteria include (i) age ≥18 years; (ii) high suspicion or pathological diagnosis of pancreatic malignancy; (iii) resectable or borderline resectable tumor before surgery, regardless of neoadjuvant chemotherapy history; and (iv) eligibility for both MI-RAMPS and O-RAMPS based on evaluation by surgeons and anesthetists before surgery.

### Exclusion criteria

The exclusion criteria include (i) suspicion or evidence of any distant metastasis or NCCN-defined unresectable arterial invasion; (ii) ASA physical status score ≥4; (iii) patient preference for a certain approach or change of willingness; and (iv) absence of malignancy based on the postoperative pathological report.

### Borderline resectable tumor

According to NCCN version 1.2020 guidelines and Isaji et al. (18), a tumor will be classified as borderline resectable if at least one of the following factors is recognized: (i) Solid tumor contact with the superior mesenteric artery ≤180° or >180° without the involvement of the aorta and intact uninvolved gastroduodenal artery; (ii) solid tumor contact with the superior mesenteric vein or portal vein of >180° or contact ≤180° with contour irregularity or thrombosis of the vein, but with suitable vessel proximal and distal to the site of involvement, allowing for safe and complete resection and vein reconstruction; (iii) carbohydrate antigen 19-9 (CA19-9) level >500 U/ml; and (iv) ECOG (19) performance status ≥2.

Although patients with borderline resectable tumors will be referred to an oncologist or multi-disciplinary team and recommended for neoadjuvant therapy, this situation will not be an independent factor for exclusion.

### Randomization

Eligible participants will be recruited from eight centers after providing written informed consent. Stratified blocked randomization between O-RAMPS and MI-RAMPS will be performed in a 1:1 ratio; Before randomization, patients will be assigned to two subgroups based on resectability: borderline resectable subgroup and resectable subgroup to perform independent stratified randomization. Patients identified as borderline resectable, as illustrated in “borderline resectable tumor,” will be assigned to borderline resectable subgroups. Otherwise, the case will be in the resectable group for randomization. The block sizes will be subjected to random variation. Randomization will be concealed from all investigators. Patients will be assigned codes by numeric randomization coding, and the study coordinator will be the only one with access to these codes. The source data will be stored digitally and kept in the central database. Randomization will be performed after the surgical plan is made and the written informed consent from patients and approval for the trial are available. Patients who rescind their decision to undergo surgery and those who do not undergo surgery will be excluded from the analysis.

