### Surgical technique

The RAMPS procedure is based on a report by Strasberg et al. (8, 9). All surgeons and their surgical teams are skilled in performing this procedure. To optimize for the best outcome, surgeons can decide to perform anterior or posterior RAMPS based on their evaluation of certain clinical cases during the surgery. Meanwhile, tiny variations in lymph node dissection and necessary extended tissue or organ resection, which are not beyond the guideline, are allowed (8, 9, 20, 21). In the MI-RAMPS group, all surgical teams can choose the appropriate general laparoscopic method or robotic techniques, such as the da Vinci^®^ Surgical System, according to their preference and availability of resources.

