### Statistics

#### Sample size calculation

The MIRROR trial has been designed as a superiority trial. We hypothesize that patients with distal pancreatic cancer who undergo MI-RAMPS have a shorter postoperative stay than those who undergo O-RAMPS. Based on our previous experience and related data on the retrospective cohorts (15, 16), the expected superiority in the length of stay in the MI-RAMPS group is 3 ± 8 days. These factors, 5% two-sided significance level (α), 80% power (1-β), and 10% drop-off rate, were considered in calculating the sample size. Accordingly, the expected sample size has been set at 250 patients (125 patients in each group).

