In this trial, RAMPS will be performed using either the anterior or posterior approach according to the scope of surgical resection, which is mainly selected according to the intraoperative assessment of the chief surgeon. However, we stratified resectability before randomization because of significant differences in treatment strategy and prognosis between patients with resectable and borderline resectable tumors. A common criterion for assessing resectability is vascular invasion. However, Isaji et al. (18) have proposed certain biological criteria (CA19-9) and performance status evaluation, which have been adopted in this study. Moreover, the MIRROR trial will include a strict pathological evaluation system to reflect the oncological outcomes of MI-RAMPS. Concerning the pathology report evaluation, we will follow the margin evaluation system proposed by the Japan Pancreas Society (30) and TNM staging by AJCC to evaluate the margins, lymph nodes, and suspicious invasion in multiple dimensions to ensure the diagnostic accuracy of the pathology report.

The primary outcome of this study will be the length of postoperative hospital stay. LOS could directly and better reflect the period between operation and postoperative adjuvant therapy. In this study, all participating centers and their pancreatic surgical teams are well-experienced in both O-RAMPS and MI-RAMPS, as well as general peri-operative management. Moreover, each center has assigned at least one senior pancreatic specialist to join the adjudication committee for supervision and consultation. Therefore, to a certain extent, we believe that based on accurate evaluation criteria, the results of the corresponding superiority of LOS will indicate that MI-RAMPS is beneficial for enhanced postoperative recovery. By validating this hypothesis, we expect to provide distal pancreatic cancer patients with a safe, minimally invasive way to get the tumor radical removal and receive the necessary postoperative adjuvant therapy timely for the best chance of survival.

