The MIRROR study is the first multicenter prospective randomized clinical trial to investigate the safety and efficacy of MI-RAMPS surgery for pancreatic body and tail cancer. Admittedly, our study is not an international multicenter study, mainly due to concerns about large differences and deviations in the discharge time among each country’s national medical insurance policies and medical systems. Sample size estimation was based on LOS retrospective data from the principal investigation center, which may not be suitable for international trials. However, the conclusions will be beneficial to the exploration of further international studies and provide a reference for the establishment of RAMPS discharge standards and subsequent adjuvant therapy indications. Certainly, we encourage and look forward to conducting an international multi-center randomized clinical trial based on the results of this study for further investigation into the safety and efficacy of MI-RAMPS.

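### Randomisation across eight centres is stratified by resectability but not by centre, and the 80% power rests on one centre's SD; the cost is modest lost precision, not bias, and is recovered by centre strata together with a centre-adjusted LOS analysis

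*Protocol article*

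**What the plan says.** The Randomization section of the protocol article sets the scheme: "Stratified blocked randomization between O-RAMPS and MI-RAMPS will be performed in a 1:1 ratio", and before that step "patients will be assigned to two subgroups based on resectability: borderline resectable subgroup and resectable subgroup to perform independent stratified randomization". The Discussion gives the reason: "we stratified resectability before randomization because of significant differences in treatment strategy and prognosis". Neither place names centre as a factor.

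The Study population section states: "This study involves eight high-volume pancreatic surgery centers in China". Under Surgical technique, teams in the minimally invasive arm choose laparoscopic or robotic surgery "according to their preference and availability of resources". Under Primary outcome, surgeons approve discharge against common criteria, LOS runs to the date of eligibility rather than the actual discharge date, and disputed cases go to an adjudication committee.

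The Sample size calculation section states that "the expected superiority in the length of stay in the MI-RAMPS group is 3 ± 8 days", with "5% two-sided significance level (α), 80% power (1-β), and 10% drop-off rate". The Discussion adds: "Sample size estimation was based on LOS retrospective data from the principal investigation center". The Statistical analysis section compares continuous outcomes by t-test or Wilcoxon test and names no centre term.

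**The concern.** Blocking within two resectability lists balances the arms overall and within each resectability group, but not within a centre. A centre with habitually short or long stays can by chance supply more patients to one arm. An unadjusted comparison carries that imbalance as extra noise in the estimated LOS difference.

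The planning SD does not count this noise. An SD from a single centre describes variation between patients within that centre. If mean LOS differs between the eight centres, the SD in the pooled trial data is larger than 8 days and the power of the stated test is below 80%. The article recognises that discharge time differs between health systems, but discusses this only between countries, not between its own centres.

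**Working it through.** **Inputs from the article.** Difference 3 days and SD 8 days (reading 3 ± 8 as difference and SD), two-sided alpha 0.05, power 80%, drop-out 10%, 1:1 allocation, eight centres.

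**Assumed, because the article gives no figure.** Between-centre SD of mean LOS, τ, from 0 to 4 days. The 8 days is taken as the within-centre SD, as its single-centre source suggests.

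**Step 1: reproduce the stated sample size.** n per arm = 2 × (1.96 + 0.842)² × 8² / 3² = 111.6, so 112. With drop-out, 112 / 0.90 = 124.4, so 125 per arm and 250 in total. This matches the article exactly and leaves no allowance for centre.

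**Step 2: power of the unadjusted test at 112 per arm.** Total SD = √(64 + τ²); SE = total SD × √(2/112); power = Φ(3/SE − 1.96). The last column repeats Step 1 with the total SD.

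| τ (days) | Total SD | SE (days) | Power | Total N for 80%, unadjusted |
|---|---|---|---|---|
| 0 | 8.00 | 1.07 | 80.1% | 250 |
| 1 | 8.06 | 1.08 | 79.5% | 254 |
| 2 | 8.25 | 1.10 | 77.7% | 266 |
| 3 | 8.54 | 1.14 | 74.8% | 286 |
| 4 | 8.94 | 1.20 | 70.9% | 312 |

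With the t distribution, power at τ = 0, 2, 3 and 4 is 79.8, 77.4, 74.4 and 70.5%.

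**Step 3: size of the chance centre shift.** Eight centre effects vary about their own mean with variance (7/8)τ², so the shift in the LOS difference has SD of about τ × √(7/8) × √(2/112). For τ = 2, 3 and 4 this is 0.25, 0.37 and 0.50 day. Simulation (224 evaluable patients, random blocks of 4 or 6, 30% borderline, 2,000 runs per setting, equal and unequal centre sizes) gave 0.23 to 0.25, 0.36 to 0.39 and 0.49 to 0.50 day. With centre strata it gave about 0.07, 0.10 and 0.14 day. The mean shift was about 0. Type I error of the unadjusted test, in a run with unequal centres, was 5.0% at τ = 2 and 5.6% at τ = 4. The median worst-centre difference between arms was 8 to 9 patients, against 2 with centre strata.

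The shift and the power loss are the same variance. At τ = 4, √(1.07² + 0.50²) = 1.18 days, and Φ(3/1.18 − 1.96) is about 72%. That is close to the table's 71%, which is slightly lower because it uses the full τ².

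**Step 4: which change restores power.** Same simulation; each range covers equal and unequal centre sizes. Monte Carlo SE is about 0.9 point (√(0.8 × 0.2 / 2000)). The adjusted model contained centre; no resectability effect was simulated.

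| Allocation strata | LOS analysis | τ = 2 | τ = 3 | τ = 4 |
|---|---|---|---|---|
| Resectability | Unadjusted | 80% | 75–77% | 71–73% |
| Resectability and centre | Unadjusted | 78–79% | 75–76% | 74% |
| Resectability | Centre-adjusted | 80–81% | 78–79% | 78% |
| Resectability and centre | Centre-adjusted | 80–81% | 77–80% | 80–81% |

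A separate simulation with 6,000 runs gave unadjusted power of 78.7, 76.7 and 74.0% with centre strata, against 77.6, 76.2 and 72.4% without. Centre strata alone gain 0 to 2 points.

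**The case against.** The strongest reply is that blocked 1:1 randomisation by resectability is a valid design and that leaving out centre is a choice, not an error. This stands as to validity. A reader might infer that the LOS comparison is biased, or that the centre shift is a harm on top of the power loss. Step 3 supports neither: the shift averages zero, type I error holds, and its SD of at most about 0.5 day is smaller than the 1.07-day sampling SE already in the plan.

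A second reply is that the power argument concerns the analysis model, which an SAP that is not shown may adjust for centre. This stands in part. Centre adjustment alone recovers most of the loss, and a reader who infers that centre strata alone would restore 80% is wrong. But the allocation scheme and the power statement are fixed in this article, and an SAP cannot alter the balance the scheme delivers.

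Third, the article works against centre differences: uniform discharge criteria, LOS counted to eligibility, adjudication of disputed cases, more than 200 RAMPS cases per centre, and senior oversight across centres. This makes 3 or 4 days less likely. It does not remove centre differences, since adjudication covers only controversial cases and the discharge criteria do not govern blood loss, margins or complications.

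Finally, the article does not state outright that blocks run across centres. That is inferred from its description of two subgroups with independent lists; crossing them with eight centres would give 16 strata.

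**Conclusion.** The point holds as a matter of precision. Resectability is the only stratification factor the article names, its LOS tests are unadjusted, and the 80% power contains no between-centre variation. The loss of power is under 1 point if centre means have an SD of up to 1 day, about 2 to 3 points at 2 days, about 5 at 3 days and about 9 at 4 days.

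These sizes rest on an assumed between-centre SD, on reading 8 days as a within-centre SD, and on the other seven centres sharing that within-centre SD. The documents do not show that the trial is underpowered in fact, only that its stated power depends on centres not differing. The change is worth making because it costs little, not because the present design is invalid.

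**What to change.** 1. In the Randomization section, stratify the central blocked randomisation by centre as well as resectability, with small blocks of randomly varied size, or use central minimisation on both factors.
2. In the Statistical analysis section or the SAP, analyse LOS with both stratification factors in the model. Items 1 and 2 belong together.
3. In the Sample size calculation section, state that the 80% power assumes an SD of 8 days from one centre with no between-centre variation, and show the sensitivity range in Step 2, including 0 and 1 day.

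The cost is one change to the randomisation list, one model specification and a sentence on power; no extra patients. There are small downsides. The 16 cells average about 16 patients (250/16), and about 8 per borderline cell if 25% are borderline, so some blocks stay incomplete. With blocks of 2, 4 and 6, simulation put the overall arm imbalance at about 3 patients on average (95th percentile 8). Within-centre blocks are also slightly more predictable in an open-label trial, which varied block sizes limit. If recruitment has begun, item 1 can apply only to later patients, but items 2 and 3 still apply in full.

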### Conversion

Conversion is defined as any case requiring additional hand-assisted approaches, except those for trocars and specimen collection, in the MI-RAMPS group (22, 23). Based on practical scenarios, the conversion will consist of reactive conversions (such as bleeding and organ perforation) and conditional conversions (such as difficult exposure, failure to proceed, and expanded tumor evasion) (22). The details about the conversion will be recorded for future analysis. According to the principle of intention-to-treat, patients who will undergo conversion will be continually analyzed in the MI-RAMPS group.

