### Primary outcome

The primary outcome is the postoperative length of stay (LOS). Experienced surgeons will be responsible for the approval of discharge based on uniform criteria (24), including (i) no need for IV fluid; (ii) performance status and organ function recovery to the preoperative state; (iii) solid diet availability; (iv) no sign of infection; and (v) acceptable incision healing and pain control. However, discharge criteria do not include prophylactic drainage removal.

Patient evaluation will be recorded on case report forms (CRF) based on the observation and medical records for every round. Once the patient is eligible for discharge, the investigator will record the condition and date for the calculation of LOS, regardless of the similarity of the actual discharge date, as it may be affected by certain non-medical factors. If the evaluation for some cases is controversial, the senior surgical adjudication committee will be consulted.

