### Long-term survival

Disease-free survival (DFS) and overall survival (OS) will be used as secondary outcomes of this study. DFS is the postoperative survival period without recurrence and metastasis of the primary tumor. OS is defined as the entire length of survival after the RAMPS procedure. All related survival information, including recurrence, metastasis, and survival status, and the subsequent anti-cancer treatment information will be acquired during the postoperative follow-up. The anticipated mean follow-up period for the survival study is 24 months.

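### Randomised patients are removed after allocation (no surgery, change of mind, benign pathology), although the trial invokes intention-to-treat and has one 10% allowance with no slack

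*Protocol article*

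**What the plan says.** The Randomization section of the protocol article places allocation after the surgical plan and consent, and so before the operation. It continues: "Patients who rescind their decision to undergo surgery and those who do not undergo surgery will be excluded from the analysis".

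The Exclusion criteria add two routes. Item (iv) is "absence of malignancy based on the postoperative pathological report", which can be known only after allocation and surgery. Item (iii) is "patient preference for a certain approach or change of willingness", and the article does not say whether it stops applying at randomisation.

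The Conversion section states: "According to the principle of intention-to-treat, patients who will undergo conversion will be continually analyzed in the MI-RAMPS group". The article names intention-to-treat nowhere else.

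Under Long-term survival, "OS is defined as the entire length of survival after the RAMPS procedure", and disease-free survival is also counted from the operation. The sample size section assumes that "the expected superiority in the length of stay in the MI-RAMPS group is 3 ± 8 days" and says that a "10% drop-off rate, were considered in calculating the sample size". It does not say which patients count as drop-off.

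**The concern.** A randomised comparison is protected only while the patients analysed in each arm are those allocated to it. Here three rules can take patients out after allocation, and they do not carry the same risk.

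- **Withdrawal or no surgery.** The Blinding section calls the trial open-label and lets patients ask for their group or quit. The surgical team has to know the approach before operating. Who leaves, or whose operation is cancelled, could therefore differ by arm, and the primary comparison could shift.
- **Benign final pathology.** The Inclusion criteria accept high suspicion of malignancy, so some benign results are foreseeable. These patients received the allocated operation and have a full record of stay and complications. Dropping them loses valid data on the primary outcome and on safety.
- **Change of willingness.** It is harmless before randomisation. After randomisation it belongs with the first group.

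There is a related gap for survival. A randomised patient who never receives RAMPS has no starting point for overall survival as defined.

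Every patient removed by these rules also counts against the same 10% allowance.

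**Working it through.** **Inputs.** From Sample size calculation: difference 3 days, SD 8 days (reading 3 ± 8 as difference ± SD), two-sided α 0.05, power 0.80, drop-off 10%, 125 per arm. From Randomization: 1:1 allocation. The article gives no rate for benign pathology, withdrawal or non-operation.

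**Step 1: reproduce the plan's figure.**
n per arm = 2 × (1.96 + 0.8416)² × 8² / 3² = 111.6, rounded up to 112.
112 / 0.9 = 124.4, rounded up to 125 per arm, 250 in total. This matches.

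**Step 2: slack in the allowance.**
125 × 0.9 = 112.5 patients per arm remain, against 112 needed. The loss that can be borne is 1 − 112/125 = 10.4%. With the t-distribution the requirement is 113, and the tolerable loss is 1 − 113/125 = 9.6%. Either way, total loss from all causes must stay at about 10%.

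**Step 3: power by total loss (two-sample t-test, 3/8 = 0.375 SD).** The loss rates are assumptions.

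| Total loss | Analysed per arm | Power |
|---|---|---|
| 0% | 125 | 84.0% |
| 10% | 112.5 | 80.0% |
| 15% | 106.25 | 77.7% |
| 20% | 100 | 75.1% |

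**Step 4: size of a possible bias (illustration with assumed figures).** Suppose a fraction x leaves one arm only, and these patients would have stayed D days less than those retained. The full arm mean is then the retained mean minus x × D, so exclusion shifts the contrast by x × D. For x = 8% and D = 4 days this is 0.08 × 4 = 0.32 days, or 0.32/3 = 11% of the design effect. For 5% and 10 days it is 0.5 days; for 10% and 10 days it is 1.0 day. If both arms lost similar patients at similar rates, the shifts would largely cancel.

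**Step 5: the rules side by side.** Conversions are kept in the allocated arm. Patients not operated on, or who withdraw from surgery, are removed. Operated patients with benign pathology are removed. The result is neither a full intention-to-treat set nor a named alternative.

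**The case against.** The strongest defence is that postoperative stay does not exist without an operation, so leaving never-operated patients out of that analysis is reasonable. The two rules together then amount to a modified intention-to-treat set: operated patients, analysed as allocated. This stands for never-operated patients, and the fix below accepts it. It does not cover benign cases, who were operated on and have the outcome.

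The article also takes steps against bias. Patients are meant to be unaware of their group during treatment, randomisation is described as concealed from investigators with codes held by the study coordinator, and pathologists and the adjudication committee are not told the arm. These steps reduce the risk. They do not remove it, because a patient may ask and leave, and the operating team knows the approach.

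Three stronger readings are tempting, and the article does not support them.

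- A reader might infer that excluding benign cases biases the comparison. Benign disease is present before allocation and is read without knowledge of the arm, so the cost is mainly precision and safety data.
- A reader might infer that these exclusions exhaust the 10% allowance, or that 250 is wrong. No rates are given, the 10% may have been meant for exactly these patients, and 250 reproduces.
- A reader might infer that a trial-wide intention-to-treat commitment is broken. The article applies the principle only to conversions, and the timing of the change-of-willingness criterion is not stated.

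**Conclusion.** The point holds in a limited form. The article itself fixes removals after randomisation, so this is more than detail left to a fuller document. Arm-related withdrawal or cancellation is possible, but its size cannot be derived from the article; the shifts in step 4 rest on invented rates and on loss in one arm only. The loss of operated benign cases is certain whenever such cases occur, and it affects precision and the safety comparison more than validity.

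On power, 80% holds only if all losses together stay at about 10%. At assumed losses of 15% to 20%, power would be 77.7% to 75.1%. Keeping operated benign patients recovers part of that loss. These figures assume a 3-day difference and an SD of 8 days.

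**What to change.** 1. Apply exclusion (iii) only before randomisation.
2. Delete (iv) as an exclusion. Analyse length of stay and complications in all randomised patients who had any operation, in the allocated arm and whatever the final pathology, and name this a modified intention-to-treat set. Give length of stay in confirmed malignancy as a sensitivity analysis, and use malignancy to restrict the R0 and lymph-node analyses.
3. Replace the exclusion sentence in Randomization: report never-operated patients by arm and reason, and add a sensitivity analysis for length of stay that assigns them a range of assumed values.
4. Measure overall survival from randomisation in all randomised patients, with confirmed malignancy as a supportive analysis. The main analysis should not be restricted by histology, because some never-operated patients will have none. Keep disease-free survival for resected patients with confirmed malignancy, since it has no meaning without resection.
5. State what the 10% drop-off covers.

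**Cost.** Mostly wording and a few added analyses; operated patients need no new data for length of stay or complications. Never-operated patients need survival follow-up, and the visit schedule is now counted from surgery. A few benign cases enter the primary set and make the population slightly more mixed, which the confirmed-malignancy analysis addresses.
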